## Abstract

**Background:**

Interest in improving care for the growing number of individuals with chronic conditions is rising. However, access to care is limited by distance, disability, and distribution of doctors. Small-scale studies in Parkinson disease, a prototypical chronic condition, have suggested that delivering care using video house calls is feasible, offers similar clinical outcomes to in-person care, and reduces travel burden.

**Methods/Design:**

We are conducting a randomized comparative effectiveness study (Connect.Parkinson) comparing usual care in the community to usual care augmented by virtual house calls with a Parkinson disease specialist. Recruitment is completed centrally using online advertisements and emails and by contacting physicians, support groups, and allied health professionals. Efforts target areas with a high proportion of individuals not receiving care from neurologists. Approximately 200 individuals with Parkinson disease and their care partners will be enrolled at 20 centers throughout the United States and followed for one year. Participants receive educational materials, then are randomized in a 1:1 ratio to continue their usual care (control arm) or usual care and specialty care delivered virtually (intervention arm). Care partners are surveyed about their time and travel burden and their perceived caregiver burden. Participants are evaluated via electronic survey forms and videoconferencing with a blinded independent rater at baseline and at 12 months. All study activities are completed remotely.

The primary outcomes are: (1) feasibility, as measured by the proportion of visits completed, and (2) quality of life, as measured by the 39-item Parkinson’s Disease Questionnaire. Secondary outcomes include measures of clinical benefit, quality of care, time and travel burden, and caregiver burden.

**Discussion:**

Connect.Parkinson will evaluate the feasibility and effectiveness of using technology to deliver care into the homes of individuals with Parkinson disease. The trial may serve as a model for increasing access and delivering patient-centered care at home for individuals with chronic conditions.

**Trial registration:**

This trial was registered on clinicaltrials.gov on January 8, 2014 [NCT02038959].

**Electronic supplementary material:**

The online version of this article (doi:10.1186/1745-6215-15-465) contains supplementary material, which is available to authorized users.

## Background

Chronic conditions affect more than 147 million Americans and account for 85% of U.S. health care expenditures [1]. By 2030, chronic conditions will affect 171 million Americans, or more than half of the U.S. population [1]. Current care for chronic conditions in the United States is costly, ineffectual, often leads to poor outcomes [1–7], and increases burden on caregivers [1, 8, 9]. Many studies have shown that coordinated, multidisciplinary specialty care delivered more frequently can reduce the incidence of acute complications of chronic illness and improve patient and caregiver quality of life [2, 4, 10–14]. Home visits - once a standard mode of care delivery [15] - and care delivered into the home have shown particular promise, especially in caring for older people [16–19]. However, access to such care is frequently limited by distance, disability, and the distribution of specialists (Figure 1), and varies with race and gender [1, 20–22]. Simple, inexpensive videoconferencing technology can alleviate these barriers and provide care to these individuals in their homes.

**Figure 1 Fig1:**
[figure not shown]
**Number of typical full-time neurologist practices that would need to open to reduce the current disparity in Parkinson disease care by 50%.** Estimates assume that a typical neurologist has 10% of office visits for Parkinson disease patients; that in one year, that neurologist sees patients every six months; and that each neurologist works full-time, five days per week, minus federal holidays and standard vacation.

As videoconferencing technology has become more available, reliable, and less expensive [23–26], interest in using telemedicine to deliver chronic illness care has been increasing [23, 27]. A 2000 Cochrane review of studies comparing telemedicine to face-to-face care concluded, among other things, that ‘Studies of effectiveness, efficiency and appropriateness of telematics applications to health care urgently need to be performed, but technology may permit provision of care which is presently not possible by conventional means’ [27]. Telemedicine interventions including videoconferencing and telemonitoring for veterans with chronic conditions [28], individuals with severe asthma [29], diabetes [30–32], and heart failure [14, 33–43] have all shown promise. In a recent analysis of telemedicine’s applications in chronic disease management, [name] reviewed studies of all forms of telemedicine intervention, including remote monitoring and telephone calls, and identified significant problems with the published literature [44]. Studies exploring the use of telemedicine to enable physicians to make virtual house calls have been conducted in a variety of conditions, but have not yet been conducted in Parkinson disease at this scale. We conducted a PubMed search using ‘telemedicine AND home AND randomized’, (336 total results), ‘randomized AND video AND home’ (241 total results), ‘virtual AND visits AND home’ (29 results), and ‘videoconferencing’ AND ‘randomized’ (168 total results), to identify randomized controlled trials reporting on uses of home-based videoconferencing and reviewed the references of [name] review [44]. Of the 774 search results and 141 studies identified by [name], a total of 16 randomized controlled trials involving remote delivery of care from a physician directly to a patient in the home were identified (Table 1). The present study will be the longest randomized, controlled trial of telemedicine for Parkinson disease of which the authors are aware.

**Table 1 Tab1:** **Randomized controlled trials involving video-based virtual house calls from physicians**

Study	Year	Sample size	Study population	Intervention(s)	Duration	Primary outcomes	Results
Dorsey ER *et al*. [45]	2013	20	Individuals with Parkinson disease	Randomized to (1) in-person care or (2) care via telemedicine	7 months	• Feasibility	• Virtual house calls were feasible
						• Quality of life	• As effective as in-person care
Fortney JC *et al*. [46]	2013	364	Individuals with depression	Randomized to practice-based or telemedicine-base collaborative care	18 months	• Clinical	• Telemedicine-based collaborative care yielded better outcomes for depressed patients
McCrossan B *et al*. [47]	2012	83	Infants with congenital heart defects	Participants randomized to (1) videoconferencing support, (2) telephone support, or (3) control	10 weeks	• Acceptability	• Clinicians were more confident in treating patients in video visits vs. telephone
						• Health care resource utilization	
							• Parents were satisfied with video visits
							• Health care resource utilization was lower in videoconferencing group
Moreno FA *et al*. [48]	2012	167	Hispanic adults with depression	Randomized to telemedicine care from a psychiatrist or usual care from a primary care physician	6 months	• Clinical	• All participants improved on clinical measures
						• Quality of life	
							• Time to improvement was shorter in telemedicine group
Leon A *et al*. [49] *	2011	83	Individuals with HIV	Randomized to (1) usual care of (2) Virtual Hospital care for one year, then crossed over after one year	2 years	• Clinical	• Satisfaction with Virtual Hospital was high
						• Health care resource utilization	
						• Quality of life	
						• Satisfaction	
							• Clinical outcomes were similar for both groups
Ferrer-Roca O *et al*. [50]	2010	800	Primary care patients referred for specialized care	Randomized to face-to-face hospital referral or telemedicine from specialist	6 months	• Quality of life	• Telemedicine care was comparable to face-to-face care
							• Diagnosis and examination to start treatment were faster in the telemedicine group
Stahl JE, Dixon RF [51]	2010	175	Patients in a general primary care practice	Interviewed face to face and via videoconferencing, order randomized	2 visits	• Satisfaction	• Patients and providers highly satisfied with videoconferencing but preferred face to face
						• Willingness to pay	
							• Technical quality of video calls had significant impact on satisfaction
Dorsey ER *et al*. [52]	2010	14	Individuals with Parkinson disease	Randomized to (1) usual care or (2) care via telemedicine	6 months	• Feasibility	• Virtual house calls were feasible
							• Virtual house calls improved disease-specific measures significantly compared to usual care.
Dixon RF, Stahl JE [53]	2009	175	Patients in a general primary care practice	Randomized to one virtual visit and one face to face visit, or two face to face visits.	2 visits	• Diagnostic agreement	• Physicians and patients highly satisfied with virtual visits
							• Diagnostic agreement between virtual and in-person evaluation was similar to comparison of two in-person evaluations
						• Satisfaction	
Ahmed SN *et al*. [54]	2008	41	Epilepsy patients	Randomized to telemedicine follow-up or conventional	1 visit	• Cost-effectiveness	• 90% of patients in both groups satisfied with quality of services
						• Cost to patients and caregivers	
							• Cost of telemedicine production was similar to patient savings
						• Satisfaction	
Morgan GJ *et al*. [55]	2008	30	Parents of children with severe congenital heart disease	Randomized to telephone or videoconferencing follow-up	6 weeks	• Anxiety	• Videoconferencing decreased anxiety levels compared to telephone and allowed better clinical information
						• Clinical	
O’Reilly R *et al*. [56]	2007	495	Patients referred for psychiatric consult	Randomized to face to face or telepsychiatry	4 months	• Clinical	• Similar outcomes were seen in both arms
						• Cost-effectiveness	
							• Telepsychiatry was at least 10% less expensive than in-person care
						• Satisfaction	
							• Both groups expressed similar satisfaction
De Las Cuevas C *et al*. [57]	2006	140	Psychiatric outpatients	Randomized to face to face or telepsychiatry	24 weeks	• Clinical	• Telepsychiatry had equivalent efficacy to face-to-face care
Ruskin PE *et al*. [58]	2004	119	Veterans with depression	Randomized to telepsychiatry or in-person psychiatrist visits	6 months	• Clinical	• Both groups were equivalent in clinical outcomes, cost, patient adherence, and patient satisfaction.
						• Cost-effectiveness	
						• Health care resource utilization	
						• Satisfaction	
Bishop JE *et al*. [59]	2002	19	Psychiatric patients	Randomized to videoconference or face to face	4 months	• Satisfaction	• Similar satisfaction observed in both groups

^*^Study evaluates an intervention that includes virtual house calls, but also includes other telemonitoring or electronic communication methodologies.

Parkinson disease is a prototypical chronic condition in which to test this health care delivery method. Like many chronic conditions, Parkinson disease has an incidence that increases with age [60], a long duration (average survival of approximately 14 years after diagnosis) that results in progressive disability [61], impairs driving ability [62, 63], burdens caregivers [64], often requires institutional care [61, 65–68], generates high health care costs to private and public payers [69], and, importantly, benefits from specialized care [12, 21, 22, 70]. However, over 40% of Medicare beneficiaries with Parkinson disease do not receive neurologic care within four years of diagnosis, and those who have not are at a yearly 14% increased risk of hip fracture, 21% increased risk of placement in skilled nursing facilities within the first year, and a 22% increased risk of death within six years compared to those who see a neurologist [21, 22]. Because many of its symptoms can be readily assessed visually, interest in using telemedicine to facilitate care began over 20 years ago [71] and has increased to the present [72]. Pilot studies using web-based videoconferencing have previously shown the efficacy, value, and acceptability of virtual house calls from specialists to people with Parkinson disease [45, 52, 73]. Virtual house calls can also incorporate multidisciplinary care and education from a team of health care providers, which has been shown to be highly effective for Parkinson disease [10, 11, 74–79]. The present study will add to understanding of the promise and limitations of virtual house calls for the treatment of Parkinson disease.

The trial was registered on clinicaltrials.gov in January 2014 (NCT02038959).

## Methods

### Trial design

We are conducting a randomized comparative effectiveness study (Connect.Parkinson) comparing usual care in the community to usual care augmented by video house calls with a Parkinson disease specialist [80]. Approximately 200 individuals with Parkinson disease and their care partners will be enrolled at 20 centers throughout the United States and followed for one year. Participants receive educational materials, then are randomized in a 1:1 ratio to continue their usual care (control arm) or usual care and specialty care delivered virtually (intervention arm). Care partners are surveyed about their time and travel burden and their perceived caregiver burden. A blinded independent rater and a study coordinator conduct baseline and end-of-study assessments. All study activities are completed remotely. The specific aims of the study are: (1) to demonstrate the feasibility of using virtual house calls to deliver specialty care into the homes of individuals with Parkinson disease who have limited access to care; (2) to show that such an approach can improve quality of life; (3) to establish that virtual house calls can enhance the quality of care; and (4) to demonstrate that this remote approach to care saves time, reduces travel, and decreases care partner burden.

To conduct the study, we have partnered with the largest Parkinson disease patient organization in the country, the National Parkinson Foundation, and formed a Patient Advisory Board with patients and patient advocates who have contributed to the design of the trial and continue to be involved with the project. Finally, we have assembled a Dissemination and Implementation Advisory Board to assist in disseminating the results of the research and drive broader adoption.

This study was approved by the Research Subjects Review Board of the University of Rochester as a coordinating center (January 2014) and an enrolling site (March 2014). As of October 26, 2014, the study has been approved at 16 sites and is under review at four additional sites (Additional file 1).

### Participants

Eligibility criteria were designed to permit broad participation in the study. Individuals with clinically diagnosed idiopathic Parkinson disease, who have access to a non-public, internet-enabled device with the capacity for videoconferencing, who are physically located in a state where a participating site investigator is licensed to practice medicine when visits are conducted, and are willing and able to provide informed consent, may enroll. Participants must also have a local health care provider (for example primary care physician, nurse practitioner) who the study team can contact to provide recommendations from the site investigators, and must live at home, in a senior housing complex or assisted living facility. Individuals who are currently hospitalized, enrolled in another telemedicine study, or who have a condition (for example, prominent psychosis) that precludes study participation will be excluded from study participation.

Care partners must be adults who are able and willing to provide informed consent to be enrolled. Their participation is optional.

### Procedures

Individuals with Parkinson disease will be recruited and enrolled remotely and sent educational materials about Parkinson disease created by the National Parkinson Foundation. They will also be asked to identify their regular care partners (friends or family members who provide regular assistance with daily activities and are not paid caregivers), who will be invited to enroll. Enrollment is completed in two parts; first, a central study coordinator reviews an interest survey and contacts interested individuals to verify their eligibility and complete a screening form, then enrolling site staff contacts the potential participant to obtain consent. Consent is obtained with a written signature on a printed consent form. All study activities are completed remotely, using email, phone, fax, mail, and videoconferencing modalities to enable individuals to participate from home. Study data are collected and managed using Research Electronic Data Capture (REDCap) tools hosted at the University of Rochester [81]. REDCap is a secure, web-based application designed to support data capture for research studies, providing an interface for validated data entry; audit trails for tracking data manipulation and export procedures, automated export procedures for seamless data downloads to common statistical packages; and procedures for importing data from external sources if needed. REDCap supports the use of electronic patient surveys and automated email invitations, which are used in this study to allow participant-completed assessments to be done securely from home, with the aid of a family member if needed. A complete schedule of activities is included in Additional file 2.

Participants who enroll will be emailed a link to download secure Health Insurance Portability and Accountability Act-compliant virtual visit software from SBR Health (Cambridge, MA, USA). The software embeds videoconferencing software from Vidyo (Hackensack, NJ, USA) that is hosted by ID Solutions (Indianapolis, IN, USA), which uses two-way encrypted video transmission to ensure privacy. SBR Health also creates a virtual waiting room that allows patients to ‘check in’ for appointments. If participants do not have access to a webcam, a Creative Labs Live! Cam Chat HD camera is mailed to them prior to their baseline assessment virtual visit. A study coordinator at the University of Rochester performs a test connection with the participants, providing technical support by phone if needed. No in-person technical support is sent to the participant’s home.

Participants will be evaluated via videoconferencing and via electronically administered surveys at baseline and at 12 months. Blinded independent raters complete remote baseline and end-of-study (12-month) assessments of Parkinson disease using the Movement Disorder Society Unified Parkinson Disease Rating Scale (MDS-UPDRS) [82] modified (excludes assessment of tone and balance) for remote assessment [83]. Individuals who the independent rater believes not to have Parkinson disease are withdrawn at the baseline visit prior to randomization. A study team member also completes a remote Montreal Cognitive Assessment (MoCA) [84, 85] at this visit. Additional baseline assessments are completed by the participant/care partner and study staff as detailed in Additional file 2. Care partners are surveyed at baseline and at the end of the study about the time and travel required to help the participant with their Parkinson disease appointments, and the perceived burden of caring for the individual with Parkinson disease. All participant-completed study assessments are completed via secure survey links sent to their email addresses using REDCap, and study teams enter data from each visit directly into the study database.

### Randomization

After the initial evaluation, participants are randomized to either continue with their usual care throughout the year or to continue their usual care and receive virtual visits from a Parkinson disease specialist licensed to practice in the state in which they reside. The randomization allocation sequence was generated by [name] using R version 3.0.2. Randomization is conducted in the study’s REDCap database after the baseline assessments have been completed and Parkinson disease diagnosis confirmed. The randomization plan is stratified by enrolling site and contains blocking to ensure approximately even distribution of control/treatment arm participants.

### Interventions

Participants with Parkinson disease are randomly assigned to either continue with their usual care or continue with usual care supplemented by virtual house calls. The care received by the usual care (control) group will be variable but will be a reflection of the status quo for Parkinson disease care in the United States. This group is free to seek out specialty care over the course of the study, and we anticipate that some may do so. Those assigned to usual care are given the opportunity to have a one-time virtual visit with a Parkinson disease specialist after their final study assessment. For the telemedicine (intervention) group, the visit schedule is set by the investigator in consultation with the patient and will include at least four virtual visits over one year. Visits are similar to regular in-person clinical visits for Parkinson disease, and investigators provide a clinical note summarizing the visit and any recommendations for treatment to the patients and their local health care providers at the conclusion of each visit.

### Outcome measures

Primary outcomes include (1) feasibility, defined as the percentage of telemedicine participants who complete at least one telemedicine visit, and the overall percentage of completed telemedicine visits, and (2) quality of life, measured by the change in the 39-item Parkinson’s Disease Questionnaire (PDQ-39) [86] from baseline to 12 months.

Secondary outcomes include quality of care, as measured by the change from baseline in the Patient Assessment of Chronic Illness Care (PACIC) [87], and time and travel savings from remote appointments, and change in caregiver burden as measured by the Multidimensional Caregiver Strain Index (MCSI) [88]. Additional secondary outcomes have been selected to determine the impact of telemedicine specialist care on Parkinson disease-specific outcomes and global quality of life. The change in Parkinson disease symptoms and signs will be assessed by the change in the MDS-UPDRS from baseline to 12 months. In addition, changes in depression and cognition, common comorbidities with Parkinson disease [89–92], will be identified as the change in the 15-item Geriatric Depression Scale (GDS-15) [93] and the MoCA. Additional quality-of-life metrics are the Patient Global Impression of Change [94] and the European Quality of Life Five Dimension Five Level Scale (EuroQoL-5D-5 L) [95]. Patient-reported utilization of health care services such as hospitalizations, emergency room visits, and visits to primary care doctors [96] will also be compared between the control and intervention arms.

### Planned statistical analyses

The aims of the study are to evaluate the feasibility, quality of life, clinical benefit, quality of care, and value of using telemedicine to deliver specialty care to patients in their home. Primary measures of feasibility will be summarized using descriptive statistics. We will consider telemedicine to be feasible if 80% of participants in the telemedicine arm complete at least one telemedicine visit, and at least 80% of all telemedicine visits are completed as scheduled. Generalized linear mixed models will be used to determine what factors affect the probability of completing telemedicine visits as scheduled.

The primary efficacy outcome measure of this study is the PDQ-39. For this outcome, we will fit an analysis of covariance model with the change in PDQ-39 from baseline to one year as the response, treatment group as the factor of interest, participating physician as a stratification factor, and baseline PDQ-39 as a covariate. A *t* test will be performed to compare the adjusted treatment group means. Secondary measures of quality of life, clinical benefit, quality of care, and value to patients and care partners will be analyzed similarly. Additional analyses will examine the relationships among outcome variables. All statistical tests will be performed at the two-sided significance level of 5%, and no corrections will be made for multiple testing.

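### The primary ANCOVA adjusts for an undefined physician factor instead of enrolling site, the randomisation stratum; whether this costs anything depends on what the factor means

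*Protocol article*

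**What the plan says.** Randomisation (Protocol article, Randomization): "The randomization plan is stratified by enrolling site and contains blocking". No other stratum is named.

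Primary model (Planned statistical analyses): an ANCOVA on the 12-month change in PDQ-39, with treatment group as the factor of interest, plus "participating physician as a stratification factor, and baseline PDQ-39 as a covariate". Enrolling site is not in the model. The secondary measures are to be handled in the same way.

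Who sees a study specialist: the intervention arm is "to continue their usual care and receive virtual visits from a Parkinson disease specialist licensed to practice in the state in which they reside" (Randomization). Controls are offered only a "one-time virtual visit with a Parkinson disease specialist after their final study assessment" (Interventions), which falls after the outcome has been measured. They may also find specialty care on their own.

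The term for the physician factor is not defined. The nearest expression is in Participants, where eligibility requires everyone, in either arm, to be "physically located in a state where a participating site investigator is licensed to practice medicine".

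**The concern.** The factor in the primary model is not the factor by which the trial randomises. Site has both arms in every stratum by construction of the blocked randomisation. A physician factor has that property only if every participant, control or intervention, is linked to a physician before allocation, and the article does not say so.

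The gap matters more here than in most trials because contact with a study physician is the intervention. If the factor records who delivered the visits, it is known only after allocation and only in one arm. Adjusting for it can remove part or all of the treatment contrast, and it conditions on something that happens after randomisation. The models at stake are the primary efficacy analysis and every secondary analysis built on the same template.

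**Working it through.** **Inputs.** From Sample size: N = 200, d = 0.5, two-sided 5%, dropout up to 20%, planned power 80 to 90%. From Trial design: 1:1 allocation and 20 centres. Derived: 200 × 0.8 = 160 completers, 80 per arm; spread evenly, 160/20 = 8 per site, 4 in each arm. The even spread is an assumption, made for simplicity. No variance reduction from baseline PDQ-39 is credited.

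**Step 1: the plan's own figure.** The noncentrality for a two-sample t test is d × √(n/2) = 0.5 × √(80/2) = 3.162. With 158 df, power is 88.2% (88.5% by the normal approximation). This lies within the stated 80 to 90%, so the plan's figure is reproduced.

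**Step 2: formula for a stratified model.** Information on the treatment contrast is the sum over strata of n1 × n0/(n1 + n0). The noncentrality is d × √information. A stratum with one arm only contributes zero.

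**Step 3: four possible meanings of the factor.**

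*(A) Site, or one site investigator linked to both arms.* Each site gives 4 × 4/8 = 2, so information is 20 × 2 = 40. The model has 1 intercept + 19 site terms + 1 baseline + 1 treatment = 22 parameters, leaving 160 − 22 = 138 df. Power is 88.1%. Nothing is lost.

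*(B) Delivering physician, with controls coded as none.* All 20 physician strata hold only intervention participants and the none stratum holds only controls. Information is 0. The design matrix has 23 columns (intercept, 20 terms for 21 levels, baseline, treatment) and rank 22. Treatment is fully aliased and cannot be estimated.

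*(C) Delivering physician, two per site, controls coded to the lead.* The number of physicians, the even split and the coding are all assumptions. Per site, the lead has 4 controls and 2 intervention participants, giving 4 × 2/6 = 1.333; the second physician has 2 intervention participants and no controls, giving 0. Information is 20 × 1.333 = 26.7. The standard error rises by √(40/26.7) = 1.22. The noncentrality is 0.5 × √26.7 = 2.58, and power is about 73%.

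*(D) Two physicians per site, both arms assigned at random before allocation, four completers each.* The number of intervention participants k in a group of four has probability C(4,k)²/70. The expected value of k(4 − k) is (16×3 + 36×4 + 16×3)/70 = 240/70 = 3.43, so expected information per group is 3.43/4 = 0.857. Over 40 groups this gives 34.3. The standard error rises by √(40/34.3) = 1.08 and power is about 83%.

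| Meaning of the factor | Information | Power at d = 0.5 |
|---|---|---|
| (A) Site, or one investigator per site | 40 | 88% |
| (D) Two per site, fixed beforehand in both arms | 34.3 | about 83% |
| (C) Two per site, controls coded to the lead | 26.7 | about 73% |
| (B) Controls coded as none | 0 | not estimable |

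**The case against.** The strongest reply is that the physician factor is simply a label for the enrolling site. Eligibility ties every participant, before randomisation, to a state in which a participating site investigator is licensed. Site staff obtain consent from controls as well, so each control already belongs to a site. The article calls the factor a stratification factor, and the only stratification it describes is by site. It also plans to compare adjusted group means, which presupposes an estimable contrast. This reading is plausible. With one investigator per site it is case (A) and does no harm; with several, all assigned beforehand in both arms, case (D) still falls inside the planned power range.

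Two further points stand. Case (B) would fail visibly when the model was fitted rather than bias a result unnoticed. And a condensed article may leave the coding of a factor to a fuller document that is not shown, so the missing definition is not in itself a fault.

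What the reply does not remove is the difference between the two statements that the article does make: randomisation by site, and a model by physician without site. The benign reading needs either one investigator per site or an assignment made beforehand in both arms, and the text states neither.

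**Conclusion.** The mismatch is in the text and affects the primary model and the secondary models patterned on it. Its consequence is conditional. It ranges from no loss, if the factor is the site's single investigator, to a non-estimable treatment effect, if it is the delivering physician and controls have none. The fall in power from about 88% to about 73% illustrates one intermediate coding; it rests on an assumed two physicians per site, an even split of intervention participants and controls all coded to the lead.

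A reader might infer that controls have no participating physician, and hence that the treatment effect is confounded with the factor. The document does not support that as a fact, because it never says the term means the clinician who makes the visits, nor how many investigators a site has, nor when participants are linked to them. The stated sample size and power are sound and are not affected under the benign reading. This is a free improvement, with moderate severity and moderate confidence.

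**What to change.** In Planned statistical analyses, replace participating physician with enrolling site in the primary ANCOVA, and state that the secondary models use the same factor. If variation between physicians is of interest, describe it separately within the intervention arm. If physician is kept in the model, define it as an assignment made for both arms before randomisation, and say how it relates to site.

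The cost is a few words. Site is already the stratum of the REDCap randomisation, so no new data are needed, and with site as the factor power at d = 0.5 stays at about 88%. The article reports recruitment as still open, so the change can be made before any outcome analysis.
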